### Sample Size

Based on a previous study [27], a mean improvement of 2.16 kg, with an estimated standard deviation of 5.2 kg, in handgrip strength is expected; therefore, a minimum of 56 participants (using power=0.8 and α=.05) are needed. When accounting for 10% dropout, a minimum of 63 participants are needed. Given that 7 participating centers are involved, each center aims to include 9 participants, but centers are allowed to include more if they can, up and until the total target sample size is achieved.

### Data Management

Prior to the start of the study, a data management plan that covers all aspects of handling data gathered during and after completion of the iHand project, such as collection, storage, back-up, documentation, access, sharing, reuse, preservation, and archiving (both at the study coordinator’s site and participating centers), was devised.

All documents related to this study and all participant data will be collected in the investigators’ site files. These files, containing personal and contact information, as well as the screening information from potential candidates, will be safeguarded at the participating center of the corresponding participants. All relevant data (participants’ characteristics and clinical assessments) will be copied from the case report form into a web-based clinical database for case report form data (Castor, Castor EDC) by site investigators using unique and anonymous participant codes. All questionnaires (Michigan Hand Outcomes Questionnaire–Dutch Language Version, Motor Activity Log, numeric pain rating scale, EQ-5D, and Short Form 36) are filled in by participants via the web-based clinical database directly on site (ie, these data are not stored in site files). One center will deviate from this procedure—the participants will fill in the questionnaires on paper. These forms are kept in the site file and the data will be entered into the Castor database by the investigator. Transcripts of the weekly phone calls with the participants during the intervention period, copies of the diaries kept by participants, and extracted glove-use data (.csv format) are sent to the study coordinator by email, with participant identification code, after completion of the study. These data will be stored in a secure location on the local computer network of the study coordinator. Personal data of the participants recruited by a particular center will not be reported in the database or in any communication beyond the center and are only accessible by the investigators from that center. If necessary, the participant can be linked to these data by a participant identification code list, which is safeguarded at each center separately. In the source document agreement, the location of personal data is described by each individual center. Participating centers only have access to their own data set. The study coordinator and monitor have access to the full data set.

All coded data will be stored for 15 years within the clinical database environment and a copy of that database will be stored at Roessingh Research and Development BV for an unlimited time period, backed up daily, after downloading the completed and closed data set from the database.

### Statistical Analysis

Outcome measures will be analyzed using SPSS statistical software (version 19; IBM Corp). Data from the 3 baseline assessments (T0, T1, and T2) will be averaged (for overall preassessment values). Statistical analysis of the therapeutic effect will be performed on all participants who completed all assessments up to and including T3 and T4. Data from participants who drop out before or during the intervention period will be analyzed separately to analyze the patient characteristics of dropouts, including the reasons for dropout, to identify potentially relevant information regarding reevaluation of target population, device-related issues, to inform proper interpretation of study outcomes.

Normality of data distribution for each outcome measure will be checked by visual inspection and with the Shapiro-Wilks test, prior to analyzing outcome measures. Descriptive statistics will be used for all outcome measures (mean and standard deviation or median and interquartile range as applicable). The overall level of significance will be set to *P*<.05.

In order to assess the effect of the intervention over time, linear mixed models will be used to analyze changes in outcome measures over time. If a significant difference is found between sessions, multiple comparisons are performed with Sidak posthoc analysis. If data are not normally distributed, logarithmic transformation will first be applied to potentially achieve normally distributed data and enable use of linear mixed models for analyses. Otherwise, the Friedman test will be used for nonparametric analysis.

In addition, correlations (Pearson correlation coefficient or the nonparametric Spearman correlation coefficient, depending on data characteristics) between amount of use (measured by diary, Carbonhand system, or Motor Activity Log) or baseline patient characteristics and change in hand function outcome measures will be calculated to evaluate whether an increased dose or specific patient characteristics are associated with better outcomes

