
## Methods

### Study Design

This study is a multicenter uncontrolled intervention trial (iHand). All participants will be assessed 5 times: 3 preassessments, 1 postassessment, and 1 follow-up assessment (Figure 1). SPIRIT (Standard Protocol Items: Recommendations for Interventional Trials) [28] will be used.

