### Study Procedure

All health care professionals involved in the study received extensive training prior to the start of the patient recruitment in order to standardize the execution of the study across the different centers. Plenary instruction sessions were scheduled; health care professionals were trained in good clinical practice, execution of the study protocol, in fitting and operating the Carbonhand system, and in explaining (following a standard procedure) the use of the Carbonhand system to the participants. All instructions were also documented in logbooks and manuals, which were provided to the professionals. The latest versions of these documents are maintained on a secure project website.

In total, there are 5 assessments for each participant. Three preassessments (T0, T1, and T2) are scheduled across 3 weeks, as baselines, directly prior to the intervention period. After completing the third baseline session, the Carbonhand system is manually adjusted by the professional to the individual participant. Attention is paid to the correct size of the glove and arm straps, the finger length of the glove, and creating 3 support profiles. In addition, instructions about all aspects of the Carbonhand system are given, demonstrated, and practiced with the participant, until the professionals are confident that the participant knows how to use the system properly at home. In addition to receiving the Carbonhand system, all participants will be provided with a short user manual (in Dutch) and an excerpt from the exercise book [30], in which exercises (functional activities that can be used in the home situation) are described for people with almost complete function of the arm.

During the 6-week intervention period, participants use the Carbonhand system at home. Within 1 week of the end of the intervention period, postassessment (T3) is conducted; 4 weeks later, a follow-up assessment (T4) is conducted, to measure the retention of effects.

Monitoring visits by an independent study monitor are planned for each participating center to ensure the continued protection of participants rights and well-being, to assure protocol adherence, and to verify data integrity during the study in compliance with good clinical practice. All protocol deviations will be filed. We anticipate having 5 monitor visits to each center during the course of the study.

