### Outcome Measures

#### Overview

The primary outcome measure of the study is maximal handgrip strength. Secondary outcome measures, related to arm and hand function, functional ability, amount of glove use, pain, and quality of life (Table 1), are only performed on the most affected side. All assessments are estimated to take 1.5 to 2 hours.

During the intervention period, the amount of glove use will be recorded automatically by the Carbonhand system. In addition, participants are asked to keep a diary about daily use of the glove and all activities in which they engage. In order to get a thorough understanding about the experience of the participants of using the Carbonhand system during activities of daily living at home and the user friendliness of the system, semistructured interviews will take place after the intervention period (T3).

**Table 1 table1:** Overview of outcome measures.

Outcome measure	International Classification of Functioning, Disability and Health component	Domain	Assessment
Maximal handgrip strength	Body function	Grip strength	T0-T4
Maximal pinch strength	Body function	Pinch strength	T0-T4
Static grip endurance	Body function	Grip endurance	T0-T4
Action Research Arm Test	Activity	Upper extremity performance	T0-T4
Jebsen-Taylor hand function test	Activity	Fine and gross hand motor skills	T0-T4
Michigan Hand Outcomes Questionnaire–Dutch version	Activity	Self-perceived health state	T0-T4
Motor Activity Log	Activity	Self-perceived upper limb performance	T0-T4
Numeric pain rating scale	Body function	Self-perceived intensity of pain	T0-T4
EuroQol 5 dimension, 5 level	Participation	Self-perceived health-related quality of life	T0-T4
Short-form 36	Participation	Self-perceived quality of life	T0-T4
Glove use data	Activity	Registered amount of use	Intervention period
Diary	Activity	Self-perceived amount of use	Intervention period
Semistructured interview	Activity	Patient’s experiences of Carbonhand use	T3

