In addition to these strengths, we face some challenges. First, the therapeutic effects of Carbonhand will be assessed using an uncontrolled design because of practical reasons—limited availability of resources in terms of project funding and project duration. Second, some outcome measures, for example those assessed with the Motor Activity Log, Michigan Hand Outcomes Questionnaire–Dutch Language Version, Short Form 36, EQ-5D, and the semistructured interview and diaries, are self-reported, which includes the risk of socially desirable answering. Potential bias is reduced as much as possible by allowing participants to complete the questionnaires by themselves, without interference from the health care professional. Finally, participants that might be disappointed about the effect of the glove may have a higher risk of dropout during or directly after the intervention period. This may influence postintervention (T3) and follow-up (T4) results. In order to prevent this effect as much as possible, professionals were instructed to explain the importance of completing the study to all participants at the start of the study. In addition, the characteristics of the dropout sample will be analyzed to inform proper interpretation of study outcomes. Another limitation is the cumulative collection of glove-use data via the Carbonhand system. This means that the exact amount of use per day per week or per bout of activity cannot be retrieved. In order to obtain insight into day-to-day use of the glove, participants are asked to note this information daily in a diary.

This is the first powered clinical trial to investigate the unique application of an assistive grip-supporting soft robotic glove for use outside of clinical settings with the aim to have a therapeutic effect. Despite the abovementioned challenges, the study will provide a solid knowledge base about the therapeutic effect of 6 weeks of home use of an assistive grip-supporting glove.

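### Averaging T0, T1 and T2 with no check of change across them leaves any practice gain before the glove unestimated and lets part of it into the T3 change

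*Protocol article*

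**What the plan says.** Study Design has no comparison group: "This study is a multicenter uncontrolled intervention trial (iHand". The Discussion repeats this as a limitation: "the therapeutic effects of Carbonhand will be assessed using an uncontrolled design because of practical reasons".

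Study Procedure places three assessments before any glove use: "Three preassessments (T0, T1, and T2) are scheduled across 3 weeks, as baselines, directly prior to the intervention period". The device is fitted only afterwards: "After completing the third baseline session, the Carbonhand system is manually adjusted by the professional to the individual participant". T3 follows within a week of the end of the 6-week period, and T4 comes 4 weeks after T3.

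Under Outcome Measures, "The primary outcome measure of the study is maximal handgrip strength". Table 1 lists it, with the other clinical tests and questionnaires, at every visit from T0 to T4.

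Statistical Analysis then fixes how the baselines are used: "Data from the 3 baseline assessments (T0, T1, and T2) will be averaged (for overall preassessment values". After that, "linear mixed models will be used to analyze changes in outcome measures over time", with Sidak comparisons if the sessions differ. The section states no test or estimate of change from T0 to T2, no contrast of T3 with T2, and no comparison of run-in change with change over the glove period. The Discussion lists the lack of a control group, self-report and dropout as challenges, but not practice with repeated tests.

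**The concern.** With no control group, a rise from before to after glove use can come from the glove, from familiarity with the tests, or from drift. Maximal grip, pinch and endurance tests and timed hand tasks are repeated at up to five visits. The stretch from T0 to T2 contains repeated testing and no glove, so it is the most direct evidence in the study on the other two explanations.

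The stated analysis merges these three visits into one value. If scores climb across them, their mean lies below the level reached just before the glove was issued, and that shortfall is added to the T3 change. The stated analysis gives no estimate by which a reader could tell whether this happened. The article nevertheless concludes that "the study will provide a solid knowledge base about the therapeutic effect of 6 weeks of home use", which attributes the change to the glove.

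**Working it through.** **Inputs.** From Sample Size: expected improvement 2.16 kg, SD 5.2 kg, 56 completers, power 0.8, alpha .05. From Statistical Analysis: averaged baseline and Sidak comparisons. Assumed, because the documents give no figure: a practice gain of d kg per session, taken as 0.25 to 1.0 kg.

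**The plan's own figure.** The test behind 56 is not named. The normal approximation (5.2 × (1.960 + 0.842) / 2.16)² gives 45.5, so 46. A two-sided paired t test needs 48. Halving alpha to .025 in the normal approximation gives 55.1, so 56. The dropout step is exact to rounding: 56 / 0.9 = 62.2, so 63. With 56 completers a plain paired t test has 86% power. Nothing below depends on how 56 was reached.

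**Bias, with zero glove effect.** Set T0 = 0, T1 = d, T2 = 2d. The averaged baseline is (0 + d + 2d) / 3 = d.

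- Practice stops at T2, so T3 = 2d. T3 minus the mean is d; T3 minus T2 is 0.
- One more step by T3, so T3 = 3d. T3 minus the mean is 2d; T3 minus T2 is d.
- If the only gain is d between T0 and T1, the mean is 2d/3, and T3 minus the mean is d/3.

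**Chance of a significant improvement.** Noncentral t with 55 degrees of freedom and noncentrality (bias / 5.2) × √56. The two-sided 5% critical value is 2.004. Sidak over three comparisons (pre, T3, T4) gives a per-test alpha of 1 − 0.95^(1/3) = 0.017, so 0.85% in the direction of improvement, with critical value 2.463.

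| d (kg) | bias (kg) | share of 2.16 kg | unadjusted (nominal 2.5%) | Sidak, three comparisons (nominal 0.85%) |
|---|---|---|---|---|
| 0.25 | 0.25 to 0.5 | 12 to 23% | 5 to 11% | 2 to 5% |
| 0.5 | 0.5 to 1.0 | 23 to 46% | 11 to 29% | 5 to 16% |
| 1.0 | 1.0 to 2.0 | 46 to 93% | 29 to 81% | 16 to 66% |

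The Sidak column ignores the requirement of an overall difference between sessions first, which could lower the rates further. Neither step changes the bias.

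**Precision of the alternatives.** Assume independent visit errors of equal variance s². T3 minus the baseline mean has variance s²(1 + 1/3) = 4s²/3; T3 minus T2 has 2s², which is 1.5 times as large. If 5.2 kg belongs to the averaged-baseline change, the SD of T3 minus T2 is 5.2 × √1.5 = 6.37 kg. Power at 56 then falls from 86% to 70% unadjusted, and to about 53% at the Sidak level. If 5.2 kg is the SD of a single-baseline change, T3 minus T2 keeps 86% unadjusted.

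T2 minus T0 also has variance 2s². Its 95% confidence interval at 56 would be about ± 2.004 × 6.37 / √56 = ± 1.7 kg, or ± 2.004 × 5.2 / √56 = ± 1.4 kg if 5.2 kg is a single-baseline SD. With d = 0.5 kg the expected T2 minus T0 is 1.0 kg, inside either half-width, so a non-significant run-in change would not show that practice is absent.

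**The case against.** The strongest reply is that the bias is hypothetical. The documents give no practice gain for grip strength. With d = 0 the averaged baseline is unbiased and more precise, which is a good reason for three baselines in a heterogeneous sample. The grip procedure (standard instructions, at least three trials, extra attempts while values rise, mean of the last three) limits familiarisation within a session, and the stable-phase criterion limits natural course. All of this stands. It does not show that d is zero between sessions, and the stated analysis does not look.

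The raw visit data are kept, descriptive statistics are promised, and the reference to differences between sessions could mean all five. So the information is absent from the stated analysis, not lost. The averaging sentence makes three levels (pre, T3, T4) the likelier reading. Planned correlations with amount of use, and T4, are further evidence within the study, but neither supplies a change without the glove.

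A reader might infer three stronger things, and the documents support none of them:

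- That the whole run-in gain counts as effect. With equal steps and a plateau at T2 only half does (d out of 2d); with a gain from T0 to T1 alone, one third does. The upper end of each range needs a further full step between T2 and T3, some 6 to 7 weeks apart.
- That averaging makes the model's standard errors wrong. This needs a single pooled residual variance, which the article does not state; under that assumption the test of pre against T3 would be conservative.
- That T3 minus T2 must replace the averaged contrast. It rests on one noisy visit, can cost substantial power, and still carries d if practice continues.

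**Conclusion.** The point holds in limited form. The stated analysis averages the three glove-free visits without examining change across them, in a trial with no other direct evidence on practice or drift. Any steady gain there enters the T3 change as d to 2d. Under the assumed 0.25 to 1.0 kg per session, that is 0.25 to 2.0 kg of the planned 2.16 kg. At d = 0.5 kg the chance of a spurious significant improvement is roughly four to twelve times nominal unadjusted (10.5 / 2.5 to 29.3 / 2.5). With Sidak the absolute rates are lower, at 5 to 16% against 0.85%.

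These figures rest on an assumed d, zero glove effect, 56 completers and SD 5.2 kg. They show what the plan could miss; they are not evidence that a practice gain exists. The averaged contrast is a defensible main analysis. What is missing is the run-in estimate needed to interpret it.

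**What to change.** In Statistical Analysis, replace the averaging step with the following:

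1. Fit the linear mixed model to all five visits, with visit as a 5-level factor.
2. Keep T3 minus the mean of T0, T1 and T2 as the main contrast, estimated within that model, to preserve power.
3. Prespecify and report beside it T2 minus T0 with its 95% confidence interval, as the change without the glove, and T3 minus T2 as a sensitivity contrast.
4. Prespecify the reading. If T2 minus T0 shows a gain, or T3 minus T2 is materially smaller than the main contrast, the full change is not attributed to the glove. Given the width of its interval, a non-significant T2 minus T0 is not evidence of no practice effect.
5. Name the comparisons that the Sidak adjustment covers. All pairs of five visits would be 5 × 4 / 2 = 10 comparisons instead of three, so the two supporting contrasts should be reported as estimates with intervals, outside that family.

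The cost is analysis wording and a few more reported lines. Every visit is already scheduled, the main contrast stays the same, and no participants are added. The Results section describes the study as still ongoing in March 2022, so at that date the change could still be specified before data collection was complete.

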Exclusion criteria were (1) having severe sensory problems of the most affected hand, (2) having severe acute pain of the most affected hand, (3) having wounds on their hands resulting in a problem when using the glove, (4) having severe contractures limiting passive range of motion, (5) having comorbidities that limit functional use and performance of the arms and hands, (6) having severe spasticity of the hand (≥2 points on Ashworth Scale), (7) participating in another study that can affect functional performance of the arm and hand, (8) receiving arm or hand function therapy during the course of the study, or (9) having insufficient knowledge of the Dutch language to understand the purpose or methods of the study. Reasons for exclusion will be reported.

Eligible candidates participate in a test session, in which the glove system is explained, the size of the glove and straps are determined, and the support of the glove is tested by performing several grasps (10-15 minutes). The aim of this test session is to allow participants to experience the support that can be expected from the glove system and make a well-informed decision about the study.

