Jebsen-Taylor Hand Function Test is a reliable and valid test to evaluate functional hand motor skills in different patient groups and healthy people of various ages [37]. The test consists of 7 different unilateral hand skill tasks related to activities of daily living: (1) writing a sentence of 24 characters, (2) turning over 7.6 cm × 12.7 cm cards, (3) picking up and moving small common objects (eg, paper clips, coins, and bottle caps), (4) stacking checkers (test of eye–hand coordination), (5) simulated feeding (eg, teaspoon with beans), (6) picking up large empty cans, and (7) moving weighted (450 g) cans. The duration of each task will be recorded in seconds and summed for the test score [38].

Michigan Hand Outcomes Questionnaire–Dutch Language Version (a total of 57 items) assesses patients’ opinions their hands and health [39,40]. The questions are used to assess out how patients feel and to what extent they are capable of carrying out daily activities in the past week (with the exception of part 3, in which the last 4 weeks is used). The problem is mapped out within 6 domains: total hand function, activities of daily living, work situation, work performance, pain, aesthetics, and satisfaction. Within each domain, items are scored on a 5-point Likert scale. The scores are normalized to a range of 0 to 100. For the pain scale, higher scores indicate more pain. For the other 5 scales, higher scores indicate better performance.

The Motor Activity Log [41] is a semistructured questionnaire that assesses self-perceived amount of use and quality of movement of the affected arm and hand by stroke patients during activities of daily living. This questionnaire consists of 26 activities and has excellent test-retest reliability for both scores of each activity; each activity is rated by the participant for quality of movement and amount of use of the upper extremity on a 5-point scale.

An 11-point numeric pain rating scale—from 0 (no pain) to 10 (the most intense pain imaginable)—is used to measure the subjective intensity of pain (patients select a value that is most in line with the intensity of pain that they have experienced in the last 24 hours). The numeric pain rating scale has good sensitivity, while producing data that can be statistically analyzed [42].

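### For skewed or bounded outcomes, the log and Friedman fallbacks appear to set a three-session average against single sessions, which can bias them with no true change

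*Protocol article*

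**What the plan says.** The Study Design section sets out "3 preassessments, 1 postassessment, and 1 follow-up assessment", so T3 and T4 are one session each. The Statistical Analysis section then says "Data from the 3 baseline assessments (T0, T1, and T2) will be averaged (for overall preassessment values").

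The main analysis is a linear mixed model over time. The fallbacks are: "If data are not normally distributed, logarithmic transformation will first be applied to potentially achieve normally distributed data and enable use of linear mixed models", and then "Otherwise, the Friedman test will be used for nonparametric analysis". The text does not say whether the log is taken before or after averaging, nor whether Friedman has three levels (pre, T3, T4) or five (T0 to T4).

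Outcomes that could plausibly reach these fallbacks include pain ("An 11-point numeric pain rating scale", with a floor at 0), the Jebsen-Taylor test (summed seconds, lower is faster) and the Action Research Arm Test (maximum 57). Table 1 lists all three at T0–T4.

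**The concern.** With no change, the Friedman test requires each participant's values to be exchangeable across the occasions compared. A mean of three sessions and one single session have the same expectation but not the same distribution. With symmetric noise this does little harm. With a floor, a ceiling or a long tail, the mean tends to fall on one side of a typical single score, and ranks pick that up as a shift. On the log scale, the log of a mean exceeds the mean of the logs, so a logged average pre-value is too high.

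The fallbacks exist for non-normal outcomes, which is where exchangeability is most likely to fail. The trial is uncontrolled, so no comparison arm would cancel the artefact, and a significant result could be hard to tell from benefit.

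**Working it through.** **Inputs.** From the protocol: three averaged pre-sessions, one T3, one T4, significance at .05 (taken as two-sided), and 56 completers (Sample Size section). The protocol gives no figure for this bias and no within-person variability for pain, timed tests or the arm test, so every distribution below is an assumption. All scenarios have no true change: T0–T4 come from the same within-person distribution.

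**1. The mechanism for pain.** Suppose pain is present on 30% of days, independently. One session is above 0 with probability 0.30. The average of three is above 0 with probability 1 − 0.7³ = 0.66. The pre-value therefore ranks above T3 more often than below it (simulated 0.49 against 0.26).

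**2. Friedman on pain, with stable differences between people.** Score = latent person level (between-person SD 2) plus session noise, rounded and cut to 0–10.

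| Latent mean / session SD | Zeros | Friedman on (average, T3, T4) | of which less pain | Friedman on five sessions |
|---|---|---|---|---|
| −1 / 1 | 75% | 12.4% | 11.0% | 4.1% |
| 0 / 1.5 | 58% | 16.9% | 15.7% | 4.6% |
| 1 / 1.5 | 42% | 11.6% | 9.7% | 4.7% |
| 2 / 1.5 | 27% | 7.5% | 5.1% | 4.7% |
| 3 / 1 | 13% | 4.8% | 2.2% | 4.5% |
| 5 / 1.5 | 4% | 4.4% | 1.1% | 4.6% |

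Other runs with stable person differences and 40–60% zeros gave about 6–14%, with 30% in one case where people differed little. A very strong person component (latent correlation 0.9) brought rejection back to about 5%. If pain comes and goes on 30% of days independently of the person, rejection is about 60%.

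**3. Log path.** For lognormal within-person noise with log-SD s, the expected log of the mean of three exceeds the mean log by about s²/2 − s²/6 = s²/3.
- s = 0.1: 0.01/3 = 0.33%
- s = 0.2: 0.04/3 = 1.33%
- s = 0.3: 0.09/3 = 3.0%

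With n = 56, the standard error of log T3 minus the mean of the three logs is s√(4/3)/√56. The bias is therefore 0.22, 0.43 and 0.65 standard errors. Simulated log-scale rejection is 5.2%, 6.6% and 9.9%; Friedman on the same data gives 4.7%, 6.4% and 8.9%. Averaging the logs instead gives 4.6–6.2% across the log scenarios.

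A plain log is undefined at pain 0. With log(x + 1), an offset the article does not mention, pain shows an apparent fall of 2.4–6.4% and rejection of 8.9–16.0%, including about 9% for mid-scale pain.

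**4. Other outcomes.**
- Arm test, latent mean 50, 54, 57: Friedman 5.1%, 6.9%, 8.8%, the excess towards improvement.
- Timed test with an occasional slow session (10–20% of sessions, 1.5–2 times as long): Friedman 19.5–28.1%, log path 7.0–10.6%, towards faster.
- Symmetric, grip-like noise: Friedman 5.7%, no direction.
- Untransformed mean contrast: about 4–7% throughout, no systematic bias.

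**5. Direction.** Friedman bias favours the glove for floored pain, slow-tailed times and a ceilinged arm test. Log bias favours it when lower is better and runs against it when higher is better, as it would for logged grip strength.

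**6. The remedy under drift.** With a one-off practice gain of 0.5 session SD after T0 and nothing later, the five-session Friedman omnibus rejects 65%, the planned three-level version 14%, and the rank contrast of T3 against the mean rank of T0–T2 16%.

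**The case against.** The strongest reply is that the order of operations is read into the text. The average could be meant for description only, and the number of Friedman levels and the log order are details that an analysis plan may settle. In part this stands: the article does not fix the order. But the averaging sentence sits in the analysis section and defines the pre-value, while descriptive statistics have their own sentence in the next paragraph. Entering the average is the natural reading, and nothing in the text prevents it.

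A second reply is that large error rates need sporadic pain unrelated to the person, whereas participants are to be in a chronic, stable phase. This stands. A reader might infer that a significant pain or Jebsen-Taylor result would probably be an artefact, with error rates of 60% or more; the documents give no variability data to support that. Nor does the exclusion for "having severe acute pain of the most affected hand" show that scores sit near zero, since people with chronic arthritis are eligible.

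A third reply is that the bias does not always favour the glove and leaves the first-line primary analysis alone. This also stands.

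Finally, simply running Friedman on five sessions would make it sensitive to drift across T0–T2. That is correct, and it shapes the fix.

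**Conclusion.** The point holds as a defect in the fallback analyses, mainly for secondary outcomes. On the natural reading, a three-session mean is ranked or logged against single sessions, and the tests can lose their nominal level with no true change. The size is conditional on assumed distributions:

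- **Pain, Friedman:** about 6–17% with many zeros and stable person differences, mostly towards less pain; nominal at mid-scale; far higher only if pain is sporadic and unrelated to the person.
- **Arm test:** small, up to about 9% at the ceiling.
- **Timed tests:** small at within-person log-SD of 0.2 or less (log bias about 1.3% at 0.2); larger if variability is greater or occasional sessions are very slow.
- **Untransformed mixed-model contrasts, including primary grip strength:** not affected.

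The documents do not support a general claim that the plan favours the glove, nor one that the primary result is at risk from this. The problem is separate from practice effects and arises with perfectly stable participants.

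**What to change.** State that the averaged pre-value is neither ranked nor logged.

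- **Nonparametric path:** rank the five single sessions T0–T4 within each participant, and test the contrast of T3 (and T4) against the mean rank of T0–T2 as the test of effect. This replaces the Friedman omnibus and should not be conditional on it. The contrast held 4–6% under no change. It does not remove a practice gain after T0 (16% in the example above), but is about level with the planned version there (14%).
- **Log path:** log each session first, then average the three logs or model the sessions directly. If pain is to be logged, state the offset.
- **Keep** the raw average for descriptive tables and raw-scale mean differences.

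The cost is wording in the Statistical Analysis section. Table 1 shows the outcomes concerned are already collected at all five sessions, and the article reports data collection as still under way.
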